### Interim analyses {21b}

No interim analysis will be performed. However, an interim analysis can be performed if requested by the safety board, e.g., should early termination of the trial be considered due to a suspicion of compromised patient safety by xenon or by other reasons.

### Methods for additional analyses (e.g., subgroup analyses) {20b}

A sub-study will be performed in patients with a delay to randomization of no more than 3 h after the start of aSAH symptoms.

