## Sample size {14}

A sample size of 100 is estimated on the basis of recent studies in aSAH patients as being able to provide 80% power with a 2-sided α level of 0.05 in order to detect a mean difference of 0.02 (SD 0.035) in the global fractional anisotropy of white matter between the xenon-treated group and the control group [44]. In addition, this mean difference is estimated to have a predictive value for DCI and poor neurological outcome. It is estimated that approximately 30% of the enrolled patients will be lost from the MRI studies, and therefore, 80 patients per group will be enrolled in this study.

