## Assignment of interventions: allocation

### Sequence generation {16a}

After screening, an eligible patient will be included in the study and randomly allocated into either the standard of care arm or the xenon intervention arm in a ratio of 1:1. Informed written consent of participation will be received from the next of kin or the legal representative of the included patient as soon as possible. Trial sites will have access to an Internet-based randomization system. Each subject will be assigned a unique study and randomization number. A block randomization approach will be stratified by the study site.

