## Statistical methods

### Statistical methods for primary and secondary outcomes {20a}

The primary outcome measure is a global fractional anisotropy of white matter of diffusion tensor imaging (DTI) as assessed in the 1st MRI. The univariate distributions of variables and the associations between variables will be described using summary statistics. Basic statistical tests (two-sample *t*-test, Mann-Whitney *U*-test, chi-square test, and Fisher exact test) will be used in the preliminary analysis to compare the xenon-treated and control groups. Kaplan-Meier curves and Cox regression analyses will be applied when examining the occurrence of end-point events. An analysis of variance of repeated measurements will be applied for normally distributed outcome variables. In the case of other types of variables, the analysis will be based on generalized linear mixed models which include comprehensive and general tools to analyze longitudinal data. General linear model for normally distributed outcomes and generalized linear models for other types of variables will be used for analyzing data at different time points. The analyses will be adjusted for age, sex, and site, and other baseline characteristics of patients will be used as covariates when needed. The adjusted analysis will be considered to be the main analysis. The statistical analysis will be based on all available data. If an analysis is based only on complete cases, it will be mentioned separately. The data will be analyzed according to intention-to-treat and per-protocol populations. The differences will be presented as mean differences with 95% confidence intervals for continuous outcomes, odds ratios with 95% confidence intervals for categorical outcomes, and hazard ratios with 95% confidence intervals in survival analyses. A two-sided statistical test with a significance level of 0.05 will be used in the statistical analyses.

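### The only delay analysis is confined to patients randomised within 3 h; it cannot show whether xenon's effect varies with delay, and it is imprecise

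*Protocol article*

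**What the plan says.** The section on methods for additional analyses {20b} consists of one sentence: "A sub-study will be performed in patients with a delay to randomization of no more than 3 h after the start of aSAH symptoms". It gives no hypothesis, no comparison with later patients and no interaction term. Under the eligibility criteria {10}, xenon must be able to start within 6 h of symptom onset, so the trial also enrols patients randomised after 3 h.

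The statistical methods section {20a} makes the adjusted analysis the main one and names age, sex and site as covariates, with other baseline characteristics added when needed. Neither delay nor a treatment-by-delay term is named. The general test rule is "A two-sided statistical test with a significance level of 0.05 will be used in the statistical analyses", and the same section promises effect estimates with 95% confidence intervals.

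The design figures in the sample size section {14} are "80% power with a 2-sided α level of 0.05" and a "mean difference of 0.02 (SD 0.035) in the global fractional anisotropy of white matter".

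**The concern.** Delay to randomisation is a sound variable for this purpose. It is fixed before allocation and is defined in both arms. The weakness lies in the method.

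A 3-h cut inside a 6-h window invites the reader to ask whether earlier treatment works better. The early subset gives an estimate for early patients and nothing to set it against. To say that an effect varies with delay, one needs the difference between effects at different delays, with its own standard error. The planned analysis does not produce that, although the data for it will have been collected.

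The subset is also much smaller than the trial. If a non-significant early result were set beside a significant whole-trial result, it could be taken to say something about the treatment window when it reflects only the smaller sample.

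**Working it through.** **Inputs from the sample size section {14}.** Difference 0.02, SD 0.035, two-sided α 0.05, power 80%. Also "A sample size of 100 is estimated on the basis of recent studies in aSAH patients", "approximately 30% of the enrolled patients will be lost from the MRI studies" and "80 patients per group will be enrolled in this study". Allocation is 1:1 {16a}.

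**Assumption.** The share *f* of evaluable patients randomised within 3 h is not in the document. It is varied from 20% to 70%, with arms taken as equal in size within the subset.

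**1. The plan's own figure.** n per arm = 2 × (1.960 + 0.842)² × (0.035/0.02)² = 48.1, so 49 per arm or 98 in total. The t-test solution is 49.05, rounded up to 50 per arm. The stated 100 is reproduced. With 160 enrolled and 30% lost, 160 × 0.70 = 112 remain evaluable.

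**2. Power inside the 3-h subset.** Two-sample t-test, standardised difference 0.02/0.035 = 0.571, n per arm = *f* × 112/2, true effect 0.02 at every delay. The CI half-width is the t quantile × 0.035 × √(2/n).

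| Assumed share ≤3 h | n per arm | Power | Real effect missed | 95% CI half-width |
|---|---|---|---|---|
| 20% | 11.2 | 25% | 75% | 0.031 |
| 33% | 18.5 | 39% | 61% | 0.023 |
| 50% | 28 | 56% | 44% | 0.019 |

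The half-width is close to or larger than the effect the trial is designed to detect.

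**3. Subset against whole trial.** In 400,000 simulated trials per setting (100 or 112 evaluable, *f* from 20% to 70%, normal approximation), with the same true effect of 0.02 at every delay:

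- The two significance verdicts disagree in about 18–61% of trials.
- Nearly all of this is the subset missing an effect that the whole trial detects (16–60%).
- The subset is significant and the whole trial is not in only 1–2%. With no effect at any delay, this pattern occurs in about 3–4%.

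**4. What the interaction term can deliver.** With delay split at 3 h, SE = 0.035 × √(2/n_early + 2/n_late), where n is per arm.

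- Lowest power in the range: 100 evaluable, *f* = 20%, so 10 and 40 per arm. SE = 0.035 × √(0.20 + 0.05) = 0.0175. Power for an interaction of 0.02 is about 21%.
- Highest: 112 evaluable, *f* = 50%, so 28 and 28 per arm. SE = 0.035 × √(4/28) = 0.0132. Power is about 33%.
- The smallest interaction detectable with 80% power is (1.960 + 0.842) × SE, about 0.037–0.049 across the range. This is roughly twice the design effect.
- An interaction of 0.02 at a 50:50 split would need 16 × (0.035 × 2.802/0.02)², or about 385 evaluable patients, for 80% power.

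A continuous delay term may gain some precision. The document gives no delay distribution from which to compute it.

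**The case against.** The strongest reply is that the section is a single sentence in a condensed article. It poses no timing question, an estimate in early patients is a legitimate exploratory aim, and an analysis plan could add an interaction term without contradicting anything. Part of this stands. No passage says that benefit is larger within 3 h. The background reports protection when xenon was given at once or 2–6 h after injury, and the consent section speaks of a 6-h limit. The point is therefore conditional: it matters if the result is to support any statement about timing. But the article does more than stay silent. It names an early-only population as its additional analysis, and that choice is better corrected before results are known.

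Three stronger readings may tempt a reader, and the document supports none of them.

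- **That the sub-study will often suggest a false early-only benefit.** If early and late patients were each tested, their verdicts would differ in about half of trials or more (49–62%) under a constant effect. No late-stratum test is planned. Against the whole-trial result, a spurious early-only finding arises in about 1–4%.
- **That the plan yields only a verdict of significant or not.** The statistical methods section promises 95% confidence intervals.
- **That an interaction test would settle the matter.** At 21–33% power for an interaction as large as the whole design effect, it would not.

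**Conclusion.** The point holds in a limited form. The planned subset analysis cannot show whether xenon's effect depends on delay, and it is too small to be read by its significance: under the design effect it would miss a real benefit in about 44–75% of trials if it holds 50% down to 20% of patients. These figures rest on 112 evaluable patients, the planned difference and SD, a constant effect, and an assumed share within 3 h.

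This is a minor improvement to an exploratory analysis. It does not touch the primary comparison, and the subset estimate is not invalid.

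**What to change.** Keep the 3-h estimate with its 95% CI as a display. Add to section {20b} a sentence along these lines: *Whether the effect of xenon varies with delay will be explored with a treatment-by-delay-to-randomisation term, delay entered as a continuous variable together with its main effect, in the main adjusted model on all evaluable patients; the interaction estimate will be reported with its 95% CI, and any statement about timing will be based on it and not on significance within the 3-h subset.*

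Keep delay to randomisation as the variable, since time to the start of xenon exists in one arm only. Label the analysis exploratory.

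The cost is one sentence and one model term, with no new data or patients. The downside is an imprecise interaction estimate, and the report should say that a null result does not exclude dependence on delay.

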### Methods in analysis to handle protocol non-adherence and any statistical methods to handle missing data {20c}

The data will be analyzed according to intention-to-treat analysis. The extent of possible missing data will be analyzed and examined, especially considering the primary outcome of the study.

### Plans to give access to the full protocol, participant-level data, and statistical code {31c}

The data of this study will be available to investigators whose proposed use of the data has been approved by an independent review committee. Individual participant data that underlie the results reported in this Article will be shared (text, tables, figures, and appendices), after de-identification, along with the study protocol. These data will be available 6 months after the article’s publication and will be available for 12 months from publication. Data can be used for individual participant data meta-analysis. Requests and proposals should be directed to [contact]. To gain access, data requestors will need to sign a data access agreement.

## Oversight and monitoring

### Composition of the coordinating center and trial steering committee {5d}

Turku University Hospital will be the coordinating center. The trial steering committee will be chaired by the principal investigator [name] and will comprise site principal investigators and one head physician or investigator from the Departments of Anesthesia and Intensive Care, Neurosurgery, Neuroradiology, Cardiology, and Turku PET Centre.

There is no Stakeholder or Public Involvement Group associated with this trial.

### Composition of data monitoring committee, its role and reporting structure {21a}

Data and Safety Monitoring Plan will be prepared and a Data and Safety Monitoring Board (i.e., independent safety committee) will be established according to the relevant Standard Operational Procedures of Turku Clinical Research Counsel; the plan and the composition of the board will be communicated with the National Committee on Medical Research Ethics (TUKIJA) before the commencement of this study.

In addition, TUKIJA will be informed about outcomes related to the responsibilities of the Data and Safety Monitoring Board and about other responsibilities defined by ICH good clinical practice (GCP).

The study monitor will visit the study center after enrollment of every 4 patients and after each 6-month interval. The study monitor will ensure that the study is complying with the GCP and applicable regulatory requirements and that the protocol is being adhered to in all aspects, with accurate recording of results, reporting of AEs, drug accountability, and record keeping.

Furthermore, it will be verified that the clinical facilities remain adequate and that the CRFs correspond with source data. For this purpose, the study monitor will be allowed direct access to hospital or patient records of the study subject, original laboratory data, etc., relevant to the study. It is essential that the investigator and other relevant members of the study center team are available during the monitoring visits and inspections, and that they can devote sufficient time to these processes.

### Adverse event reporting and harms {22}

Study subjects participating in this study are already in need of intensive care due to one or more signs of organ insufficiency or failure. Therefore, multiple and diverse clinical symptoms and laboratory findings must be anticipated to occur frequently. Expected minor fluctuations in the study patients’ presenting illness will not represent an AE. Any clinically significant worsening in a study patient’s condition according to clinical judgment, laboratory finding, or other diagnostic findings, compared with the study patient’s baseline status at the time of starting xenon treatment will have to be recorded as an AE whether or not the worsening condition is considered to be due to the study patient’s underlying illness or study treatment. All AEs must be elicited, documented, and reported to the investigator from the moment of treatment until the end of the follow-up period of six months.

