### Trial design {8}

The Xe-SAH study is a prospective, multicenter phase II drug intervention trial. The study design is a single-blind, prospective superiority randomized two-armed parallel follow-up study. The primary objective of the study is to explore the potential neuroprotective effects of xenon, when administered within 6 h of the initial insult, in adult (≥ 18 years of age), mechanically ventilated aSAH patients with a Hunt-Hess grading of 3–5. There are two study arms: the control arm receiving the current standard of care while the intervention arm will be administered a 24-h xenon treatment in addition to the standard care.

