### Secondary outcome measures

Fractional anisotropy of white matter at cerebellum and/or at corpus callosum as assessed with the 1st MRI.Safety and tolerability of xenon, as assessed with a ratio of adverse events, serious adverse events, and suspected unexpected serious adverse reactions (SUSARSs) during the follow-up at 1 year between the xenon group and the control group.Composite of radiological EBI (within 72 h after the start of SAH symptoms), DCI, cerebral infarction (see definitions in detail under the section of secondary objectives) and poor outcome (good: mRS 0–2; poor: mRS 3–6) at 3-months and at 1 year.Neurogenic stress cardiomyopathy and stunned myocardium (i.e., myocardial injury caused by sympathetic storm and autonomic dysregulation with hs-troponin elevation, left ventricular dysfunction or ECG changes)ICP-level up to 14 days (i.e., as long as clinically relevant) after the onset of aSAH symptomsNeed for ICP therapies up to 14 days (i.e., as long as clinically relevant) after the onset of aSAH symptomsDuration of therapy for ICP control/monitoring up to 14 days (i.e., as long as clinically relevant) after the onset of aSAH symptomsPlasma catecholamine levelsDifference in selected biomarkers (NSE, NF-L, GFAB, S100B, UCH-L1, total-tau TNF-α, interleukins 6 and 10) and difference in metabolomic and lipidomic profiles in the blood and CSF between xenon and control group in predicting risk for EBI, vasospasm, DCI as well as a good neurological outcome at 3 months, 1 year, and at 2 years after the aSAH.Development of prognostication models with a selected combination of brain imaging and biomarkers obtained from various MRI techniques (see details under the section “Data collection and management”), clinical data, and metabolomics (see details under the section “Data collection and management”) by applying artificial intelligence and machine learning for EBI, vasospasm, DCI, and a good neurological outcome at 3 months, 1 year, and at 2 years after the aSAH.Difference in CTA, DSA, and MRI parameters obtained from various MRI techniques (see details under the section “Data collection and management”) between xenon and control group in predicting EBI, vasospasm, DCI, and a good neurological outcome at 3 months, 1 year, and at 2 years after the aSAH.Predictive value of computational fluid dynamics (CFD) (see details under the section “Data collection and management”) to detect the differences in the blood flow behavior in the recruited patients by applying 3D DSA to assess the risk of EBI within the first 72 h after the start of aSAH symptoms, vasospasm (within 21 days after the start of SAH symptoms) and DCI (between day 4 and 6 weeks after the start of SAH symptoms) and a good neurological outcome at 3 months, at 1 year, and at 2 years after the aSAH (mRS 0–2).Difference of metabolomics and lipidomics profiles of plasma and CSF between xenon and control group and in predicting the risk for EBI within the first 72 h after the start of aSAH symptoms, vasospasm (within 21 days after the start of SAH symptoms) and DCI (between day 4 and 6 weeks after the start of SAH symptoms) and a good neurological outcome at 3 months, at 1 year, and at 2 years after the aSAH (mRS 0-2).Difference of activity of microglial cells between the subjects in the xenon and control groups and in predicting the risk for DCI and a good neurological outcome at 3 months, 1 year, and at 2 years after the aSAH.

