### Implementation {16c}

The Xe-SAH -trial comprises the following scheduled events: screening, ICU stay (treatment induction and maintenance and post-treatment), hospital stay after ICU stay, and follow-up at 3, 12, and 24 months after the SAH. In order to confirm the feasibility of the protocol (i.e., period of feasibility), the trial will be initiated in the intensive care unit of Turku University Hospital in close liaison with the Departments of Neurosurgery and Neuroradiology. We expect that the period of feasibility will be completed within 3–6 months. Thereafter, the trial will also be started in Tampere and Kuopio University Hospitals. Implementation will be the responsibility of the senior physicians and researchers from the Departments of Anesthesiology and Intensive Care, Neurosurgery, and Neuroradiology at each participating center.

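### The safety outcome is defined at 1 year but adverse events must be reported only to six months, and the adverse-event baseline exists only for patients who start xenon

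*Protocol article*

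**What the plan says.** Five places in the protocol article bear on this.

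- **Secondary outcome measures.** The second outcome opens with "Safety and tolerability of xenon, as assessed with a ratio of adverse events, serious adverse events". SUSARs complete the list of events, and the period and comparison are given as "during the follow-up at 1 year between the xenon group and the control group". It is a comparison between arms with a 1-year horizon, and the summary is called a ratio.
- **Objectives.** The matching secondary objective speaks of the incidence of the same three kinds of event, not a ratio.
- **Adverse event reporting and harms {22}.** AEs are to be elicited and reported "from the moment of treatment until the end of the follow-up period of six months". A clinically significant worsening "compared with the study patient’s baseline status at the time of starting xenon treatment will have to be recorded as an AE", whether or not it is attributed to the study treatment.
- **Implementation {16c}.** The scheduled events after the hospital stay are "follow-up at 3, 12, and 24 months after the SAH".
- **Trial design {8}.** The arms are "the control arm receiving the current standard of care while the intervention arm will be administered a 24-h xenon treatment" on top of standard care. Controls receive no xenon.

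**The concern.** A between-arm safety comparison needs one observation window, and a starting point that is defined for every patient in both arms. Here the outcome and the reporting rule give different end dates, and the rule that decides what counts as an AE refers to an event that happens in only one arm.

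Safety and tolerability is a declared outcome of this phase II drug trial. If sites follow the reporting section, they may stop recording at six months, and later events may be hard to recover when the 1-year comparison is due. An analysis plan cannot repair that, because it cannot analyse events that sites were not required to record. On the baseline, sites would have to choose their own reference time for controls, and the immediate care providers are not blinded to arm.

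**Working it through.** The document gives no computed figure for the safety outcome, so this check sets the sections side by side. The only computed figure is the sample size for the primary endpoint, and I reproduced it to confirm that it is separate from this point.

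**Sample size (context only).** Inputs from Sample size {14}: difference 0.02, SD 0.035, two-sided α 0.05, power 80%.
- Normal approximation: n per arm = 2 × (1.960 + 0.842)² × (0.035 / 0.02)² ≈ 48.1, so 49 per arm or 98 in total.
- The t-test version gives 49.05, so 50 per arm or 100 in total, as stated.
- With 30% lost from MRI, 80 × 0.70 = 56 evaluable per arm, which exceeds 50.

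None of this depends on AE collection.

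**End of the window.**

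| Item | End | Section |
|---|---|---|
| Safety outcome | 1 year | Secondary outcome measures |
| Required AE reporting | six months | Adverse event reporting and harms {22} |
| Scheduled patient follow-up | 3, 12, 24 months | Implementation {16c} |

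Share of the outcome window with required reporting = 6 / 12 = 50% of calendar time. The remaining six months fall outside required reporting in both arms. The 6-month interval under Frequency and plans for auditing trial conduct {23} concerns monitor visits, not patient contacts, so it does not supply the missing time point.

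**Start of the window and reference status.** The reporting section uses two separate phrases, which should be kept apart.
1. Reporting starts at the moment of treatment. This is loose and could be read as the start of either arm's allocated care.
2. Worsening is judged against status when xenon starts. This names xenon explicitly.

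Applying the second phrase to each group:

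| Group | Has a xenon start time? |
|---|---|
| Xenon arm, treatment started | yes |
| Xenon arm, never started | no |
| Control arm | no |

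The middle group matters because the statistical sections call for an intention-to-treat analysis, which keeps those patients in the xenon arm.

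Randomisation and xenon start are also different moments. Allocation follows screening, which takes place in the emergency setting. Xenon begins on admission to intensive care, with the ICP monitor already in place (Intervention description {11a}). The document does not give the length of that interval. The 6 h limit in the eligibility criteria runs from symptom onset to xenon start, so it is not a measure of the time from randomisation to xenon.

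**SUSARs.** The abbreviation list expands the term as a suspected adverse reaction. If that means a reaction to the study drug, which is an assumption because the article does not define it further, controls have none. A literal xenon-to-control ratio would then have a zero denominator. If *ratio* means a proportion within each arm, as the word *incidence* in the objectives suggests, the control value is simply zero and nothing is undefined.

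**The case against.** The strongest reply is that this is a mismatch of dates, not a lost outcome. Six-month AE data would exist in both arms. The modified Rankin score, whose worst category is death, is collected at 1 year. The reporting section sets a duty to elicit events and does not forbid recording at the 12-month contact. The 50% is calendar time, not events: the 24 h exposure, the ICP outcomes (up to 14 days) and delayed ischemia and infarction (up to 6 weeks) all lie well inside six months. The schedule figure is not available here, and a condensed article may leave arm-specific safety rules to the full protocol or to the separate Data and Safety Monitoring Plan.

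Much of this stands, and it rules out several stronger readings.

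- A reader might infer that the safety outcome cannot be produced at all. The document does not support that. What fails is full observation of the outcome as defined.
- A reader might infer a bias in favour of xenon, with early events absorbed into baseline in the xenon arm and counted in controls. That needs an earlier origin for controls, and none is stated. Control events could equally be under-recorded, which would bias against xenon.
- A reader might treat 6 h as the size of the excluded interval. As shown above, that limit measures something else.
- A reader might call the SUSAR comparison undefined. That depends on taking *ratio* literally.

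Two things do not yield. The two end dates are both explicit, and nothing in the text reconciles them. The xenon-start baseline is a stated rule that fails for one arm, not a detail left for another document.

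**Conclusion.** The point holds as an internal inconsistency in two parts. First, the outcome runs to 1 year while required AE reporting stops at six months, a time with no scheduled follow-up, so 6 of 12 calendar months are covered. Second, the reference status for an AE exists only for patients who start xenon, so the arms have no common baseline. The share of events affected, and the size and direction of any bias, cannot be determined from the document. The SUSAR wording is a minor matter.

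This rests on the article text as it stands and on the assumption that the schedule figure contains no AE rule that overrides it. It should be fixed, but it is not critical: it affects one secondary outcome and leaves the primary endpoint and sample size untouched.

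**What to change.** 1. Reconcile Secondary outcome measures with Adverse event reporting and harms {22} on one end date. Either collect SAEs to the existing 12-month contact or restate the outcome as six months. If only SAEs are extended, state the end date for non-serious AEs separately, so that each component has a matching window.
2. Use randomisation as time zero and as the reference status for AEs in both arms. This also covers patients assigned to xenon who never start.
3. Replace the ratio with the proportion of patients with at least one AE, and with at least one SAE, compared by arm regardless of causality. This agrees with the incidence wording in the objectives.
4. As a wording point, report SUSARs descriptively for the xenon arm.

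The cost is protocol wording and changes to dates on the case report form. If 12 months is chosen, it adds a small SAE query at a contact that already exists. The sample size does not change.
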